## Abstract

**Background:**

Suicide is a substantial public health concern for countries worldwide. Effective preventive and curative interventions for self-harm behavior (SHB) are imperative for nations with an alarmingly high rate of suicide and self-harm behaviors. The intervention protocol named *FASE (Family and Social Engagement)* consists of comprehensive assessment, Attachment-Based Family Therapy (ABFT), and community linkages for people presenting with suicide or self-harm in emergency departments of tertiary hospitals.

**Methods:**

This article reports the design and protocol for a cluster randomized control trial for suicide prevention and management. After the developed intervention is pilot tested in a tertiary hospital in Kerala, the intervention will be scaled up to be implemented in various tertiary hospitals in Kerala. Each hospital emergency department will be considered a cluster, and these clusters will be randomized to the intervention group and control group in a 1:1 ratio. The eligible people from the intervention clusters will undergo a baseline assessment, a structured moderate intense intervention with twelve sessions spread across 6 months by the trained social workers supervised by the Mental health team, and a follow-up assessment at the end. Participants will be recruited after obtaining consent and explaining the study. The primary outcome includes suicidality measured by the Depressive Symptom Inventory–Suicidality Subscale (DSI-SS), Depression, Anxiety and Stress Scale (DASS), MOS Social Support Survey, and Brief resilience scale (BRS).

**Discussion:**

Knowledge generated from this trial can significantly affect new programmatic policy and clinical guidelines that will improve the reduction of suicide rates in the country.

**Trial registration:**

Prospectively registered in Clinical Trial Registry India (ICMR-NIMS) on 18/10/2021 (ref number- REF/2021/10/048264).

## Introduction

Suicide is a global and significant public health concern worldwide, and its prevention has become a priority on the international public health agenda. Moreover, an aspirational Sustainable Development Goal (SDG) of a one-third reduction in the suicide death rate (SDR) by 2030 (1) compels the member nations to initiate proactive steps to achieve the global targets. The preventive measures are more important in Southeast Asia, accounting for roughly 40% of the estimated 800 000 annual suicide deaths globally. India has the highest suicide rate in South East Asia (2). Furthermore, India has the third-highest female suicide rate of 14.7%, and 71% of them are done by individuals below 44 years (2) imposes a substantial social, economic, and political burden on society. There are indications that for each adult who died by suicide, more than 20 others may have been attempting suicide (3). For each suicide, approximately 135 people are affected with intense grief or other emotional problems (4). Despite these galvanizing rates, India's suicide preventive intervention programs are not promising due to slow coordination at the national and state levels (5, 6). However, the recent decriminalization of suicide in India's Mental Healthcare Act (7) is a proactive step, making the government duty-bound to provide care, treatment, and rehabilitation, instead of penalizing the individual who has attempted suicide.

Alarmingly high suicide rates, global commitments, and paradigm shifts in government policies in India call for an urgent yet well-coordinated suicide prevention and management model to consider the issue of suicide a priority condition. Though the study of suicide and suicidal behavior has been approached from various theoretical models, including cognitive (8, 9) and dialectical behavior (10, 11) models, they often have little clinical efficacy or direct application in the Indian context. There is considerable evidence of the significance of family involvement (12) and increased family support (13) in reducing the risk and facilitating the management of suicidal thoughts and behaviors in individuals. The FASE model is designed as a family-based intervention due to the collectivist mindset of the Indian population. Attachment-based family therapy (ABFT) is a psychological component of the intervention to rebuild meaningful relationships and resolve family ruptures (14). Further, the social and economic issues are dealt with by utilizing the untapped family resources and customizing the pathways or linkages to community resources (15). Therefore, the proposed model consists of an indicated suicide prevention model comprising of patient engagement, ABFT, and formal and informal family and community resource linkages with 1 to 6 months of low-intensity monitoring and follow-up.

The comprehensive mental health assessment and active post-hospital psychosocial care by appropriately trained personnel are the primary prevention strategy to reduce future suicidal ideation and self-harm (16). As a secondary prevention strategy, the project clinicians will provide ABFT with a specific focus on strengthening family involvement. Community linkage with formal services such as government and employment; informal services like non-government and voluntary organizations; community health services, social support service agencies, and financial aid will act as the tertiary and rehabilitative strategy within the model. Thus, this intervention can provide various levels of prevention to people with self-harm behaviors. None of these elements has previously been combined to intervene for suicidal or self-harm behaviors in the Indian population.

This study will be conducted among an identified at-risk and vulnerable group of people presented at emergency. Existing evidence shows that the effective management of self-harm Behavior (SHB) to reduce the risk of subsequent suicide must be an essential element of suicide prevention strategies since self-harm is the most potent risk factor for future suicide (17).

## Materials and methods

### Aim of the study

The research has two aims, to build evidence on the effectiveness of an Attachment-Based Family Therapy and Resource linkage model to prevent suicide in people presenting with self-harm behaviors in emergency departments at tertiary hospitals in Kerala; Secondly, to evaluate the efficacy of the process of delivery of services and assess the cost-effectiveness of sharing the care task with the social work trainees supervised by the mental health team, through a continuum of care from critical health care to family-based services. The research team has been developing this model for over the past 2 years. The results of this feasibility trial would provide insights into the model's effectiveness in responding to multiple and complex psychological and social precipitants to deliberate self-harm that are currently ignored in general health services.

### Objectives of the study

The major objectives of the study include

Evaluate the contribution of psychosocial factors to self-harm behavior and the role of psychosocial aspects in preventing suicide.Develop the ABFT and Community Linkage model for the prevention of suicide in a group of people presenting with self-harm behavior at emergency departments;Compare the treatment (TAU) as the usual plus FASE intervention with the TAU using a cluster RCT design framework;Develop the systems and processes appropriate to deliver the services for people presenting with self-harm behavior at emergency to integrate a psychosocial intervention that would have broad relevance and application nationally and in low and middle-income countries;Assess the proposed model's cost-effectiveness for managing self-harm behavior focused on a seamless continuum of care from acute health to community services.

### Trial design

The study involves three phases;

Phase 1: development of a family-based intervention with the three components, Comprehensive psychosocial assessment and assertive engagement, Attachment-Based Family Therapy (ABFT), and community resource linkages.Phase 2: the feasibility trial of the developed intervention, andPhase 3: the cluster randomized control trial of suicide prevention intervention among randomly selected tertiary hospitals in Kerala.

In phase one, the development of intervention components includes a need assessment survey followed by a rapid systematic review of the preventive interventions for suicide and self-harm. A qualitative and quantitative need assessment was conducted among 44 patients who presented with self-harm behaviors in a tertiary hospital in Kerala between October and December 2020 (results submitted elsewhere). The rapid systematic review and the assessment findings guided the components of the intervention. In the second phase, the developed intervention will be tested for feasibility and effectiveness in a tertiary hospital in Kerala using a pre-post interventional design. Phase three comprises the experimental trial of the finalized care package using a cluster-randomized trial in different tertiary hospitals in Kerala.

### Study setting

A list of NABH (National Accreditation Board for Hospitals and Healthcare) Accredited hospitals from Kerala state, India, will be prepared to select the intervention clusters. The inclusion criteria for selecting hospitals will be any NABH accredited Tertiary referral multi-speciality hospital with a minimum of 500 inpatient beds. Eligible hospitals will be randomized to intervention or control groups in a 1:1 allocation ratio. We will sign a referral agreement with the emergency department in charge and their team after explaining to them the purpose. Emergency departments of the chosen hospitals will be considered as individual clusters, and all those who presented to the emergency departments of these hospitals after serious suicidal attempts will be assessed by the professional social workers working in the department. The Social Workers will induct the people and their family members after educating them about the purpose of the study and getting informed consent. The consented people from the experimental cluster will receive the treatment as usual (TAU) plus FASE intervention, and the people belongs the control clusters will receive the treatment as usual (TAU) interventions. The stages of enrolment, intervention, and assessment can be seen in Figure 1.

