### Outcome

Study outcomes are assessed at baseline and 6-month follow-up. Demographic characteristics measured at baseline include age, gender, marital status, education, occupation, and family income. The following information on the clusters selected will be collected: number of hospital beds, patients, social workers, primary treatment modalities, and the average length of stay at the hospital. Measurement domains and time points are summarized in Table 1.

**Table 1 T1:** Measurement domains and data collection time points.

**Variable**	**Dimensions included**	**Measurement tool**	**Data collection time points**		
			**Baseline (T0)**	**3 months (T1)**	**6 months (T2)**
Demographic assessment	Age, sex, marital status, education, occupation, and family income		✓		
Suicidality	Suicidal thoughts and ideation	Depressive Symptom Inventory–Suicidality Subscale (DSI-SS)	✓	✓	✓
Depression, anxiety, stress	Depression, anxiety, stress	DASS 21	✓	✓	✓
Social support	Emotional support, tangible support, affectionate support, positive social interaction	The MOS social support survey	✓		✓
Resilience	Resilience	The Brief Resilience Scale (BRS)	✓		✓
Customer satisfaction		Questionnaire			✓

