### Statistical analysis plan

#### Sample size and power calculation

A sample size of 282 will be collected from 10 clusters, with an average of 28 required from each of the 10 clusters. The clusters receiving the FASE intervention and the clusters receiving the usual care will be randomized 1:1 ratio and 28 samples will be recruited for the study allowing for a 20 % loss in follow-up rate. The Critical z is 1.64 and *R*^2^ is 0.3 with 95% power, a two-sided alpha of 5% with a cluster effect of 0.05 results in a sample size of 256. The 95% power and additional 10% respondents would allow us to maintain at least the 80% power even after the 20% loss to follow-up. Thus, we aim to recruit 282 participants for this study.

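### The article describes 1:1 randomisation of eligible hospitals before the referral agreement, does not make agreement a condition for allocation, and states no balancing rule for 10 clusters

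*Protocol article*

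**What the plan says.** The Study setting section starts from a list of accredited Kerala hospitals that "will be prepared to select the intervention clusters". Eligible means "any NABH accredited Tertiary referral multi-speciality hospital with a minimum of 500 inpatient beds". It continues: "Eligible hospitals will be randomized to intervention or control groups in a 1:1 allocation ratio". The next sentence is: "We will sign a referral agreement with the emergency department in charge and their team after explaining to them the purpose". Assessment, consent and treatment of patients follow.

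The Trial design section calls phase 3 a "cluster randomized control trial of suicide prevention intervention among randomly selected tertiary hospitals in Kerala". There is therefore also a selection step, and its place relative to agreement and allocation is not given.

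The sample size section says "A sample size of 282 will be collected from 10 clusters, with an average of 28 required from each of the 10 clusters" and repeats the ratio: "The clusters receiving the FASE intervention and the clusters receiving the usual care will be randomized 1:1 ratio". It allows for 20% loss of participants and makes no allowance for loss of a hospital.

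The Outcome section lists data to be collected on each cluster: "number of hospital beds, patients, social workers, primary treatment modalities, and the average length of stay at the hospital". The article gives these data no role in allocation or in the treatment comparison. The Data analysis section mentions only a discriminant analysis of whether clusters differ on the predictors.

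**The concern.** There are two separate issues, with different consequences.

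**Order of agreement and allocation.** The unit randomised is the eligible hospital, and eligibility rests on accreditation, type and bed count. Willingness to take part is not among the conditions. The two arms ask different things of a hospital. In the intervention arm its social workers deliver the two face-to-face sessions and its mental health team supervises trainees (Table 2, Human resource). In the control arm it gives usual care and the assessments. A hospital that knows its arm can therefore have an arm-specific reason to decline. The hospitals that remain are then no longer comparable by design, and dropping or replacing the ones that refuse does not restore the randomisation.

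**Balance.** Hospitals above the 500-bed floor have no upper size limit, and usual care depends on the hospital. With so few units, an unrestricted 1:1 split will often give arms that look unlike each other. The data that could prevent this are already due to be collected.

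**Working it through.** **Inputs.** From the sample size section: 10 clusters, 1:1, base 256, target 282, about 28 per cluster, cluster effect 0.05 (read here as an intracluster correlation). Inferred: 5 versus 5. Assumed, because the article gives no figure: the refusal rate per hospital, the effect size, and the distribution of hospital size.

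**The plan's own figure.** 256 × 1.10 = 281.6, rounded up to 282, and 282 / 10 = 28.2 per hospital. This last step reproduces. The base of 256 cannot be checked, since no effect size or SD is stated.

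**Loss of a hospital after allocation.**
- One of five is 20% of an arm's clusters. Cluster-level degrees of freedom fall from 10 − 2 = 8 to 9 − 2 = 7.
- 282 − 28.2 = 253.8, already below the base of 256 before any participant is lost, unless other hospitals recruit more.
- Chance that at least one of 10 refuses = 1 − (1 − q)^10:

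| Assumed refusal rate q per hospital | At least one refusal |
|---|---|
| 5% | 40% |
| 10% | 65% |
| 20% | 89% |
| 30% | 97% |

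- Power of a two-sided cluster-level t-test at an assumed d = 0.6. The variance is [0.05 + 0.95/28] × (1/k1 + 1/k2) = 0.0839 × (1/k1 + 1/k2).
  - 5 versus 5: 0.0839 × 0.40 = 0.0336, 8 df, power 81.7%.
  - 4 versus 5: 0.0839 × 0.45 = 0.0378, 7 df, power 75.4%.
  - 4 versus 4: power 68.6%.
- Worst-case selective refusal, where the hospital with the most extreme true level in one arm always drops out. The between-hospital SD is √0.05 = 0.224 outcome SD. By simulation the arm difference shifts by about 0.065 SD for one such refusal and 0.12 SD for two.

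**Imbalance if allocation is unrestricted.**
- Number of 5:5 allocations: C(10,5) = 252.
- At least four of the five largest in one arm: 2 × [C(5,4) × C(5,1) + C(5,5) × C(5,0)] = 2 × (25 + 1) = 52, and 52/252 = 20.6%.
- For a normally distributed hospital factor, the difference between two means of five has SD √(2/5) = 0.63. P(|difference| > 0.5 SD) is about 43% and P(> 1 SD) about 11%. The mean difference is zero.
- These two percentages depend on the distribution. For a factor that is simply large or small, five of each, the SD is 0.527. A 3–2 split differs by 0.2/0.527 = 0.38 SD and a 4–1 split by 0.6/0.527 = 1.14 SD. Then 20.6% of allocations exceed 0.5 SD, and the same 20.6% exceed 1 SD.
- On the outcome scale: if a factor explained all between-hospital variation, a 0.5 SD imbalance would move the arm difference by 0.5 × 0.224 = 0.11 outcome SD.
- Restricting to 3–2 splits on size leaves 2 × C(5,3) × C(5,2) = 200 allocations, so a constraint still leaves ample randomness.

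**The case against.** The strongest reply is that the order is only the order of sentences. The article never says that agreement comes after allocation. The same paragraph defines emergency departments as clusters after the randomisation sentence, so it is not strictly chronological. Agreement might sit in the random selection step, and the referral agreement may not be the hospital's consent to the trial at all. Figure 1 could not be read for this check and may settle the sequence. This stands in part: a reader might infer that the plan commits to randomising hospitals that have not agreed, and the text does not state that. But the paragraph otherwise runs in time order, and agreement is nowhere a condition for allocation, so a team following it as written would allocate first.

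A reader might also infer that the article plans simple randomisation. It does not say so. It gives only the ratio, and a condensed article may leave stratification to the full protocol. Silence on this alone would be weak ground, which is why it comes second here.

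Nor does size imbalance bias the comparison. Its expectation over allocations is zero, and a cluster effect in the sample size already represents between-hospital variation. The word bias belongs only to the refusal route, where the worst case above is modest for one hospital.

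Finally, it can be said that adjusting for a balancing factor spends the scarce degrees of freedom it is meant to protect. That is fair, and it is the reason to restrict on one factor and not several.

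**Conclusion.** The point holds as a weakness in the procedure as written. Read in its own order, the Study setting section allocates hospitals that have not agreed and lets refusals depend on the arm. The size of that risk depends on a refusal rate the article does not give. At an assumed 10% per hospital, the chance of losing at least one is 65%. One loss takes a fifth of an arm and, at an assumed d = 0.6 with a correlation of 0.05, lowers power from 81.7% to 75.4%. The possible bias from one wholly selective refusal is about 0.065 SD.

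The balance issue is secondary and conditional on unrestricted allocation. The 21% figure is exact for 5 versus 5; the 43% figure needs a normally distributed factor. The consequence is lost precision and a less credible single allocation.

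It deserves attention before allocation, because arm-dependent refusals cannot be undone afterwards. If agreement already comes first in practice, one sentence resolves the main part.

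**What to change.** State the sequence in the Study setting section:

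1. All 10 hospitals sign the agreement to take part before allocation and before any arm is disclosed.
2. The hospital data listed in the Outcome section are collected at that stage.
3. Hospitals are randomised 1:1 with stratification or a constraint on one factor, for example beds or self-harm volume. Beds are already on the list; self-harm presentations would have to be added, since the list names only patients.
4. Arms are then disclosed.
5. The primary analysis accounts for the chosen factor.

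Also say where the random selection of hospitals falls in this sequence, and how a hospital that withdraws after allocation will be handled.

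The cost is earlier collection of hospital data, a short allocation program, and about one cluster-level degree of freedom (8 to 7 with 10 hospitals).

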**Figure 1 F1:**
[figure not shown]
Consort flow diagram.

### Participant recruitment

A feasibility trial will be performed in one of the clusters among patients presenting with self-harm behaviors at their emergency department. Social workers under the supervision of the head of the department of critical care and emergencies in the hospital and the project lead will form a multidisciplinary team to run the project. Professional social workers employed in the hospital are responsible for recruitment, baseline and follow-up assessments, and initial interventions. The mental health team will confirm the caseness of each potential participant after scrutiny of the filled-up assessment framework. The disagreements, if any, will be sorted out by the confirmatory assessment by the mental health team. As part of their field placement, a pool of social work trainees from the social work institutions across the State will deliver the follow-up telephonic interventions. Baseline and 6-month follow-up assessments will be performed using a set of standardized questionnaires. After completing the 6-month-long feasibility trial, the intervention will be tested in the emergency departments of randomly selected clusters.

Criteria for the participants of the cluster-randomized trial include:

The participants should fulfill the standard definition of suicide attempt: “An act with a non-fatal outcome, in which an individual deliberately initiates a non-habitual behavior that without intervention from others will cause self-harm, or deliberately ingests a substance above the prescribed or generally recognized therapeutic dosage, and which is aimed at realizing changes which the subject desired *via* the actual or expected physical consequences” (18).

Inclusion criteria is as follows:

Patients presenting with attempted suicide or self-harm behaviors at emergency departments of the selected hospitals will be included.We will include patients with age over 18 with non-habitual deliberate self-harm, and serious suicide attempts admitted to the emergency section or emergency rooms within 14 days of their index attempt to get treated for their physical issues.We will include the patients with chronic medical conditions (especially dreadful diseases), in the study, assuming that despite their constant contact with the medical facility and frequent hospital admissions due to their physical conditions, the system insensitivity could result in patients slipping through the mental health or suicidal ideation detection gateways.

Exclusion criteria for the patients include:

We will exclude the patients with parasuicidal pauses and parasuicidal gestures to ensure the groups' homogeneity to test the intervention's effectiveness.Patients who do not have a consenting family member to participate will be excluded.We will exclude patients admitted to the psychiatric wards 14 days after the index attempt and the patients with schizophrenia spectrum disorders, severe bipolar, and severe dementia, assuming that they would require inpatient and intense care to manage their disorders, and this will prevent confounders and mixed-effects (19).Considering the huge treatment gap for mental disorders in India (20), the newly detected patients with serious mental disorders would be excluded from this study and will be referred to the psychiatric facility for necessary pharmacological and intense psychotherapeutic interventions.

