### Study procedure

The initial phase would focus on developing a collaborative family approach within the unique cultural milieu of Kerala, India, to maximize acceptability. The team will perform the forward/back-translation of standardized scales and indexes into the local language (Malayalam). This phase would also involve the development of an accompanying fidelity scale to guide and test the implementation of the ABFT model in the selected population so that mediators for good outcomes could be evaluated. Social Work Trainees (SWTs) supervised by the professional mental health team consisting of a psychiatrist, clinical psychologist, psychiatric social workers and psychiatric nurses would assess and provide intervention. The mental health team has supervisory, trouble-shooting, and evaluative functions. Social worker trainees would record qualitative observations regarding processes and outcomes to complement the measurement tools to enhance the overall evaluation. Focus group discussions would also be employed to review progress and address any treatment issues. The feasibility trial phase would last up to 6 months until SWTs demonstrated reasonable competence in the use of measurement tools and the intervention packages. The last phase will involve a cluster-randomized trial with a targeted sample size of 158 people who has SHB presenting at emergency departments at selected clusters in Kerala. The ABFT model will be implemented bi-weekly for 6 months, and the results will be compared with a treatment-as-usual (TAU) comparison group (medical management).

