#### Primary outcome

The primary outcome will be the total suicidality score measured by the Depressive Symptom Inventory–Suicidality Subscale (DSI-SS) (21). The DSI-SS is a 4-item self-report questionnaire designed to assess the frequency and intensity of suicidal ideation and impulses in the past 2 weeks. The scale measured suicidality on a four-point scale ranging from 0 to 3, with higher scores indicating greater severity of suicidal ideation. DSI-SS scores exhibited good internal consistency, ω = 0.90 [95% CI =0.89–0.91], convergent validity (rs = 0.52–0.74), discriminant validity (rs = 0.12–0.27) (22).

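### The article is inconsistent on who assesses participants, and under either reading the role that collects self-reported suicidality also delivers part of FASE in intervention hospitals only

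*Protocol article*

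**What the plan says.** Two sections of the protocol article assign assessment, and they differ.

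- Participant recruitment gives it to hospital staff: "Professional social workers employed in the hospital are responsible for recruitment, baseline and follow-up assessments, and initial interventions". The same section says that "a pool of social work trainees from the social work institutions across the State will deliver the follow-up telephonic interventions".
- Study procedure says of the social work trainees: "supervised by the professional mental health team consisting of a psychiatrist, clinical psychologist, psychiatric social workers and psychiatric nurses would assess and provide intervention".

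Table 2 divides delivery of the 12 sessions. Social workers give the 2 direct hospital sessions. Supervised trainees give the 8 family-therapy sessions and the 2 linkage sessions by telephone.

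For the cluster trial, Study setting says that people presenting at the emergency departments "will be assessed by the professional social workers working in the department", and that these workers also enrol them and take consent. Allocation is by hospital: "Eligible hospitals will be randomized to intervention or control groups in a 1:1 allocation ratio". The section on the control group promises the same instruments in both groups but does not say who administers them.

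On the primary outcome the article says: "The DSI-SS is a 4-item self-report questionnaire designed to assess the frequency and intensity of suicidal ideation".

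**The concern.** In a FASE hospital, whoever delivers FASE knows the arm, because the whole hospital is allocated. If the same role also collects the 3- and 6-month questionnaires, patients there report suicidal thoughts to the role that has been helping them. Patients in control hospitals report to staff who have delivered no FASE session. The circumstances of measurement then differ between arms in exact step with allocation.

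A short self-report of suicidal ideation is sensitive to who asks and who will see the answers. A difference produced in that way cannot be told apart from a treatment effect at the analysis stage, since the two are fully aligned. The DASS, MOS and BRS are questionnaires too and share the exposure. At stake is whether a modest DSI-SS difference could be read as an effect of FASE.

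**Working it through.** **Roles side by side**

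| Role | Delivers in FASE hospitals (Table 2) | Assesses according to |
|---|---|---|
| Hospital social workers | 2 of 12 sessions, direct | Participant recruitment; entry assessment in Study setting |
| Social work trainees | 8 + 2 = 10 of 12 sessions, by telephone | Study procedure |

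On the first reading, the assessing role delivers 2 of 12 sessions. On the second, it delivers 10 of 12. On neither is outcome collection separate from delivery. No section names a third role for the cluster trial. Using the same instruments in both groups does not address who receives the answers.

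**Size, as an illustration only**

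The article gives no figure for such a bias, so there is none to reproduce. The shifts b below are assumptions.

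Inputs from the sample-size section: 282 participants, 10 clusters, 20% loss to follow-up, two-sided alpha of 5%, and a cluster effect of 0.05, which I read as an ICC (an assumption).

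- Analysed: 282 × 0.8 = 225.6, or 22.56 per cluster.
- Design effect: 1 + (22.56 − 1) × 0.05 = 2.078.
- Standard error of the arm difference in SD units: √(4 × 2.078 / 225.6) = 0.192.
- Normal rejection rate with no true effect: Φ(b/0.192 − 1.96) + Φ(−b/0.192 − 1.96).
- With 10 clusters in two arms, a t reference with 10 − 2 = 8 df is more apt. The rate then comes from the noncentral t with noncentrality b/0.192.

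| Assumed shift b (SD) | b/SE | Normal | t, 8 df |
|---|---|---|---|
| 0 | 0 | 5% | 5% |
| 0.1 | 0.52 | 8.2% | 7.5% |
| 0.2 | 1.04 | 18% | 15% |
| 0.3 | 1.56 | 35% | 28% |

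Without attrition (282, 28.2 per cluster), the design effect is 1 + 27.2 × 0.05 = 2.36 and the standard error is √(4 × 2.36 / 282) = 0.183. The rates become 8.5%, 19% and 37% (normal) or 7.7%, 16% and 30% (t, 8 df).

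Study procedure gives a different target of 158. With 15.8 per cluster, the design effect is 1 + 14.8 × 0.05 = 1.74 and the standard error is √(4 × 1.74 / 158) = 0.210. The same shift would then mislead somewhat less often, though in the same way.

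**The case against.** The other side has substantial points.

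- **Which phase.** The Participant recruitment sentence stands in a paragraph that opens with the single-site feasibility trial, which is pre-post and has no arms. Carrying those roles into the cluster trial is an inference. It is a reasonable one: Study setting keeps the social workers as entry assessors there, Table 2 keeps the delivery roles, and nothing names anyone else. It still falls short of an explicit statement.
- **Same role, not same person.** A reader might infer that each FASE patient is assessed by his or her own therapist. The article does not say so. Duties are given to groups, and the number of social workers per hospital is ambiguous in the cost section. On the Participant recruitment reading, the assessing role delivers only the two opening sessions and none of the family therapy.
- **No rater judgement.** The DSI-SS is self-report, so biased scoring by an assessor is not the mechanism. What remains is response bias, and its strength depends on whether the worker asks for or sees the answers, which the article does not state.
- **Direction.** A reader might infer that bias in FASE's favour is built in. The documents do not support that. FASE encourages open communication, and greater trust could raise disclosure of ideation and work against FASE. Control-hospital social workers also meet and enrol their patients.
- **Condensed article.** Masking procedures may stand in a fuller protocol, so silence on masking is not itself a finding.

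All of these limit the claim. They do not remove the disagreement between the two sections, or the fact that each combines assessment with delivery.

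**Conclusion.** The point holds in limited form. The article disagrees with itself on who assesses, and each version places assessment and part of FASE delivery in one role that knows the hospital's arm. This is a stated overlap of duties. With a self-reported primary outcome, it can produce arm-dependent response bias that no analysis can remove.

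A favourable direction is plausible but not established, and neither sign nor size can be derived from the documents. If the shift were 0.1, 0.2 or 0.3 SD towards FASE, the 5% test would reject about 7.5%, 15% or 28% of the time with no true effect (t, 8 df), or 8%, 18% or 35% by the normal approximation. These figures rest on the assumed shifts, an ICC of 0.05, 226 analysed and 10 clusters. The conclusion also assumes that the stated roles carry over from the feasibility phase. The matter should be settled before outcome data are collected.

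**What to change.** 1. Reconcile Participant recruitment with Study procedure, and state one outcome-collection role for the cluster trial.
2. In both arms and by the same mode, obtain the 3- and 6-month DSI-SS and DASS and the 6-month MOS and BRS in one of two ways:
   - self-completed and returned out of sight of the treating worker; or
   - collected by an existing social worker who did not treat that patient, for example by exchanging lists between hospitals, and who is not told the arm where that is feasible.
3. Leave the plan's existing referral route to the mental health team as it is.
4. Report the remaining lack of masking as a limitation. Patients know what care they received, so separating the roles reduces response bias without abolishing it.

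The cost is some coordination between hospitals and occasional unblinding when patients mention their care. With 10 hospitals, full assessor masking may fail, and an exchanged list may reach a worker from another FASE hospital. Separating the person who treats from the person who collects is still worthwhile in that case.
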